The evaluation of the predisposition of the individual with local inflammation to develop systemic diseases can be assessed through the detection of salivary mucins, which play an important role in the protection of buccal mucosa against mechanical and microbial aggression, and the residual saliva presenting higher amounts of mucins compared to total saliva. Recently, the correlation between salivary glycoprotein expression (MUC1, MUC5B, and MUC7) and buccal candidiasis has been suggested. These glycoproteins are responsible for the lubrication and protection of the oral tissues; they also can act in the modulation of the response of microorganisms [19, 20].

Glycosylated transmembrane mucins, such as MUC1, are known as the second line of defense, possibly acting as sensors for any disturbance in the environment, signaling this information into the cell [20, 21], and interacting with local bacteria [22], acting as a barrier for opportunistic infections, against several bacterial strains. At this time, the microorganisms of the dental biofilm are disseminated into the systemic circulation, through the invasion of the gingival tissue throughout the ulcerated epithelium [23]. Also, several proinflammatory cytokines, produced by local inflammation, can reach the systemic circulation [24]; thus, justifying the correlation between stomatitis and systemic diseases.

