Saliva samples will be collected to evaluate salivary parameters. The non-stimulated total saliva will be collected for 10 min by the method of spitting, which will be analyzed for viscosity and pH measured. The calibration of pH will be performed in a pHmetro (PHTEK, Curitiba, Paraná, Brazil) after calibration of the equipment. The kinematic viscosity of saliva will be measured using a glass viscometer, and the liquid viscosity coefficient will be calculated according to Shekhar et al. [31]. The total stimulated saliva will be collected for 5 min using the habitual chewing of 1 g of gum base [19], from which the calculation of saliva volume will be obtained to evaluate the salivary flow. Subsequently, saliva samples will be centrifuged at 10,000 × g for 15 min at 4 °C, to remove cellular debris. Aliquots of supernatant will be stored at − 80 °C for the analysis. The precipitates will be evaluated by ELISA [22] to identify and quantify MUC1 expression. The absorbance at 405 nm will be measured after 30–45 min in an ELISA reader.

As a control, wells without saliva will be used. The assay for saliva will be performed in triplicate, and the results will be presented as the mean difference between optical density (OD) readings in experimental and control wells. Salivary concentrations of cytokines (IL-6 and TNF-α) will be measured using ELISA kits (Multiplex Human Cytokine Magnetic Bead Kit (Millipore, USA) according to the manufacturer’s instructions [32]. The determination of C-reactive protein in saliva will be performed using CRP ELISA kits (Salimetrics Europe Ltda.) [33]. Both ELISA methodologies will be performed in duplicates on two standard 96-well microplates, according to the protocol provided by the respective suppliers.

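### MUC1 is reported as an uncalibrated optical density with a 30–45 minute read window over several plates, and the saliva fraction assayed needs reconciling

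*Protocol article*

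**What the plan says.** All the assay rules stand in the Protocol article, Methods, Secondary outcomes, Local parameters.

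- **Preparation:** "saliva samples will be centrifuged at 10,000 × g for 15 min at 4 °C, to remove cellular debris". Then: "Aliquots of supernatant will be stored at − 80 °C for the analysis".
- **Fraction used for MUC1:** "The precipitates will be evaluated by ELISA [22] to identify and quantify MUC1 expression".
- **Reading:** "The absorbance at 405 nm will be measured after 30–45 min in an ELISA reader".
- **Blank and scale:** "As a control, wells without saliva will be used". Samples are run in triplicate, and "the results will be presented as the mean difference between optical density (OD) readings in experimental and control wells".

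In the same section, IL-6 and TNF-α are described as concentrations. MUC1 is the analyte left on an OD scale.

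Three other places matter. The Background says: "Glycosylated transmembrane mucins, such as MUC1, are known as the second line of defense". The Abstract lists MUC1 expression among the response variables, while the primary outcome under Study outcomes is stomatitis remission. Trial status gives 3 September 2018 as the start of recruitment and says the MUC1 assays are still to begin.

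**The concern.** There are two separate issues.

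**Scale and read time.** An OD has no unit of its own. It depends on how far the colour reaction has run and on how each plate behaves. The stated rule corrects it only with wells that contain no saliva, and it lets the reading fall anywhere in a 15-minute window. If the samples need several plates, two ODs from different plates are not necessarily on the same scale. Part of a patient's change from baseline to day 10, or part of the spread within an arm, could then come from the plate rather than from MUC1.

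**Fraction.** The spin is described as a cleaning step, the supernatant as the part that is kept, and the precipitate as the part that is assayed. A laboratory following the text cannot be sure which material to use. If it is the precipitate, the OD reflects how much material was spun down as well as how much MUC1 that material carries, and blank wells do not correct for the amount.

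At stake is the reading of a named secondary outcome, which the Background uses in its argument linking local inflammation to systemic disease.

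**Working it through.** The plan gives no figure for this assay that could be reproduced, so the check covers plate count, what the blank removes, the effect of read time, and the sentences on the fraction.

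**1. Number of plates.** Inputs: 4 groups of 25 = 100 participants (Planned interventions); 2 visits, baseline and day 10 (Abstract); triplicate wells (Local parameters). The 96-well format is stated for the cytokine and CRP kits and is assumed here for MUC1.

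- 100 × 2 × 3 = 600 sample wells.
- 600 / 96 = 6.25, so at least 7 plates before any control well.
- If only the 21 per group named in Sample size estimation were assayed: 84 × 2 × 3 = 504; 504 / 96 = 5.25, so at least 6 plates.

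The assay spans several plates either way. The remark about two microplates in the same section follows the cytokine and CRP kits and refers to duplicates, so I do not apply it to MUC1.

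**2. What the blank removes.** Take a simple model (assumption) for sample i on plate j read at time t:

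- sample well: OD = b(j) + g(j) × f(t) × c(i)
- well without saliva: OD = b(j)
- difference: g(j) × f(t) × c(i)

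The background b(j) goes. The plate factor g(j) and the development factor f(t) stay and multiply the result. Dividing by a common reference sample on the same plate, treated in the same way, gives c(i) / c(ref), and both factors cancel.

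**3. Size of the read-time effect.** The article gives no kinetics, so this is a range under assumption. It compares the same sample read at 45 and at 30 minutes, the two ends of the window.

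- Linear development: 45 / 30 = 1.50.
- Saturating development, ratio = (1 − exp(−45k)) / (1 − exp(−30k)), k per minute:
  - k = 0.005: 1.45
  - k = 0.01: 1.40
  - k = 0.03: 1.25
  - k = 0.05: 1.15
  - k = 0.10: 1.04

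A less extreme summary: if read times were spread evenly over 30 to 45 minutes and development were linear, the added coefficient of variation would be (15 / √12) / 37.5 = 4.33 / 37.5 = 11.5%.

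**4. Noise or bias.** Suppose a patient's MUC1 does not change. With both visits on one plate and one read time, the factor is common and the change is zero. With the visits on different plates, the apparent relative change is the ratio of the two factors minus 1, at most 50% from read time under the linear assumption. If the factor is unrelated to arm, it widens the spread in every arm and does not shift the comparison between arms. It shifts a comparison only if plates or read times line up with arm or with visit.

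**5. The fraction, side by side.** The stated purpose of the spin is to clear debris. The only saliva fraction said to be stored is the supernatant. The only sentence naming a fraction for MUC1 names the precipitate. Since recruitment began in 2018 and the MUC1 assays had not started when the article was written, the material for them must have been kept. The article does not say that precipitates were kept.

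**The case against.** **The pellet may be the intended fraction.** The Background and the Abbreviations describe MUC1 as transmembrane, so cell-associated material is a reasonable target. The section can be read coherently: supernatant kept for IL-6, TNF-α and CRP, precipitate used for MUC1 by the cited method. This stands. A reader might infer that MUC1 is being measured in waste and that the assay should move to the supernatant. The documents do not support that step: nothing ties the supernatant to MUC1, and the cited method cannot be checked here. What remains is that the sentences need reconciling and that a pellet OD is not corrected for the amount of material.

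**Cleaning effects are largely shared.** Palate brushing and denture brushing are prescribed in all four groups. A general reduction in shed material would affect all arms, so only a differential effect would distort the randomised comparison, and none is shown. This also stands. That pellet OD simply follows debris is a possible inference, not something the article shows.

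**The OD is not raw.** It is a triplicate mean with a blank subtracted, and relative OD can support a comparison between arms. True, but the comparison is clean only when plates are comparable or balanced over arms.

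**The window may be a tolerance.** All wells of a plate may be read together, and nothing says that timing differs by arm or visit. This is why the effect is called mainly noise.

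**An article leaves bench detail elsewhere.** A standard, a reference sample or a plate map may exist in the cited method or the full protocol, so their absence here is weak evidence. The point rests instead on what is stated: the OD scale, the 30–45 minute window and the two sentences on fractions.

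**Conclusion.** The point holds as a weakness in a stated measurement rule for one secondary outcome. MUC1 will be expressed as a blank-subtracted, uncalibrated OD over at least 7 plates for the full planned sample, with a read window that by itself could change the OD of the same sample by a factor of about 1.04 to 1.50. The upper figure needs linear development and the two extreme read times; the lower figure is strongly saturating development. The likely consequence is extra noise, about 11.5% under the even-spread linear assumption. Bias follows only if plates or read times differ by arm or visit, which the article neither states nor rules out.

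The sentences on the saliva fraction sit badly together and must be reconciled. They do not show that the precipitate is wrong. If it is intended, its OD mixes MUC1 expression with the amount of material spun down.

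The primary outcome and the sample size are unaffected.

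**What to change.** Before the MUC1 assays are run:

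1. Set one fixed read time for all plates.
2. Put one pooled-saliva reference, prepared as the same fraction as the samples, in triplicate on every plate, and report each sample relative to it.
3. Place both visits of a participant on the same plate.
4. Balance the four arms over the plates.
5. State which fraction is assayed for MUC1 and why, and whether the precipitates were kept. If it is the precipitate, normalise the result to its amount, for example to total protein.

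The layout fits. With three reference wells and, as an assumption, three blank wells per plate, 96 − 6 = 90 wells remain, that is 90 / 3 = 30 samples or 15 participants with both visits. Seven plates then hold 7 × 15 = 105 participants, enough for 100, with 3 or 4 participants of each arm on each plate.

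The cost is a plate map, a few wells per plate and a result expressed as a ratio to the reference instead of an OD; normalising a pellet adds one protein measurement per sample. The Ethical considerations section routes protocol changes through the Research Ethics Committee, so a change that goes beyond laboratory instruction would take that step.

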##### Characterization of the sample

Socio-demographic characteristics of the study participants will be collected from medical and dental history reports during the first consultation. Information will be collected such as length of time of edentulism, age of the prostheses in use, drug profile, hygiene habits (use of oral antiseptics or chemical hygiene of prostheses, frequency of hygiene of the prostheses), continuous nocturnal use of prostheses, and smoking.

The quality of life associated with oral health will be evaluated by applying the Oral Health Impact Profile questionnaire, specific for edentulous patients (OHIP-EDENT), validated for the Brazilian population [34]. The questionnaire presents 19 questions in four domains: “complaints related to chewing”, “psychological discomfort and incapacity”, “social incapacity”, and “pain and mouth discomfort”. Participants will be asked to answer questions about how they feel using one of the following responses: “never”, “sometimes”, or “almost always”.

Patient satisfaction will be assessed by the frequency of specific symptoms, such as local pain, burning sensation, bad breath, and buccal dryness. The responses will be collected based on a 100-mm visual analog scale (VAS), which will provide parameters for assessing heterogeneity of the eligible sample at baseline. They will also be asked to give an open-label response to other sensory side effects [10, 29]. The quality of life associated with oral health and patient satisfaction will be collected at baseline and at 10 and 30 days after treatment with the hygiene protocols (Fig. 1).

During clinical examination, the condition of the prostheses in use, such as stability and retention according to Anastassiadou et al. [28], and biofilm deposits and visible debris, will be observed [11]. Data on the shape ridge and resilience of mucosabe collected. The data on quality of life related to oral health, quality of the prostheses, and general satisfaction will be collected for the characterization of the sample at baseline [29].

### Sample size estimation

Sample size for the quantitative outcomes was determined based on the primary outcome of this study (denture-related stomatitis remission). According to a previous trial [11], we used standard deviation of 2.19 (group 1 - saline group) and 1.79 (group 2 - sodium hypochlorite), a 95% confidence interval (bilateral), and a detectable difference of at least 2 logs. Based on power of 80%, this clinical study requires at least 21 participants. An additional 20% will be added to the planned sample to compensate for possible dropouts, thus resulting in a total of 25 participants.

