**Material/design:**

A clinical trial, randomized, double-blind, and with parallel groups, will be conducted in Brazil The sample will consist of 100 patients without teeth in both arches, users of at least maxillary complete dentures, and diagnosed with DS, who will be allocated to groups (*n* = 25 per group) according to the different hygiene protocols: (1) brushing of the palate and immersion of the prosthesis in 0.25% sodium hypochlorite solution (positive control); (2) brushing of the palate and immersion of the prosthesis in 0.15% triclosan solution; (3) brushing of the palate and immersion of the prosthesis in lactose monohydrate; or (4) brushing the palate with citric acid and immersing the prosthesis in lactose monohydrate. The response variables will be heart rate variability and alteration of blood pressure (systemic level), remission of DS, removal of biofilm, reduction of microbial load (colony-forming units (CFU)), mouth and prosthesis odor level, expression of MUC1, proinflammatory cytokines, C-reactive protein (CRP), viscosity, pH and salivary flow (locally); patient-centred qualitative analysis will also be undertaken. Measurements will be performed at baseline and 10 days after the interventions. The results obtained will be statistically analyzed as pertinent, with a level of significance of 0.05.

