### Study outcomes

#### Primary: denture-related stomatitis remission

To evaluate the effect of the hygiene protocols on DS remission, the participants will be examined under the baseline condition and also 10 days after starting their specific use of the protocol. To quantify the inflammation, standardized photographs of the palate will be obtained (Digital Camera, Canon EOS, Canon EF 100 mm/2: 8 Macro Lens and Canon ML3 Circular Flash), with the focus centered on the median raphe region. The images will be transferred to the computer and two blinded, previously trained researchers will assign scores according to the classification of Kabawat et al. [10].

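### The 80% power is credited to DS remission, but the inputs are on a log scale and do not give the stated 21 per group

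*Protocol article*

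**What the plan says.** The Sample size estimation section of the protocol article begins: "Sample size for the quantitative outcomes was determined based on the primary outcome of this study (denture-related stomatitis remission". From a previous trial (reference 11) it then takes "standard deviation of 2.19 (group 1 - saline group) and 1.79 (group 2 - sodium hypochlorite", and it sets "a 95% confidence interval (bilateral" and "a detectable difference of at least 2 logs". At 80% power it arrives at 21, and adding 20% for dropout brings this to 25. The section does not say per group, but the Abstract and Planned interventions have four groups of 25, so 21 and 25 are read here as group sizes.

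Under Study outcomes, the primary outcome is DS remission at 10 days. The palate is photographed and "two blinded, previously trained researchers will assign scores according to the classification". Eligible patients have DS type IB, II or III on a modified Newton classification. Microbial load, counted as colony-forming units (CFU), is a secondary outcome under Local parameters.

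The Abstract describes the first arm as "0.25% sodium hypochlorite solution (positive control". Planned interventions lists the others as triclosan immersion, citric acid immersion, and citric acid for both immersion and palate brushing. The Abstract names a different immersion product for groups 3 and 4. That must be reconciled separately, but neither description contains a saline arm.

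**The concern.** The section names one outcome and calculates on another. A class read from a photograph has no log unit, so a 2-log difference with these standard deviations cannot describe it. The article gives no remission rate, no score standard deviation and no target score difference, so nothing else in it supports 80% power for DS remission.

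The standard deviations also come from a saline and a hypochlorite group. In this trial hypochlorite is the control and nobody receives saline. All arms also share palate brushing, denture brushing with soap and leaving the denture out at night. The section does not say why a difference of 2 logs is plausible or relevant between arms like these.

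The power statement is what a reader uses to judge how much a non-significant comparison of the primary outcome tells them. As written, it attaches a precision to that outcome that was never calculated.

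**Working it through.** **Inputs.** From Sample size estimation: standard deviations 2.19 and 1.79, difference 2 logs, two-sided 5%, power 80%, stated result 21, raised to 25. From the Abstract and Planned interventions: 25 per group, four groups. For DS remission or score: no planning values are given.

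**1. Reproducing the stated figure.**

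- Pooled SD = √[(2.19² + 1.79²)/2] = √[(4.7961 + 3.2041)/2] = √4.0001 = 2.00.
- n per group = 2 × SD² × (1.960 + 0.842)² / 2² = 2 × 4.00 × 7.849 / 4 = 15.7, so 16. Solving with the t distribution gives 16.7, so 17.
- The article states 21. Its dropout step follows from that: 21 × 1.2 = 25.2, given as 25.

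**2. Power that the stated group sizes have for 2 logs.** Normal approximation: Φ[(2/2.00) × √(n/2) − 1.960].

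| n per group | √(n/2) | minus 1.960 | Power, normal | Power, t-test |
|---|---|---|---|---|
| 21 | 3.240 | 1.280 | 90% | 89% |
| 25 | 3.536 | 1.576 | 94% | 93% |

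**3. What would give 21.** Three variants come near it, and the section states none of them:

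- 90% power: 2 × (1.960 + 1.282)² = 21.02.
- 80% power with a Bonferroni correction for three comparisons: 2 × (2.394 + 0.842)² = 20.94.
- SD 2.19 in both groups: 2 × 4.7961 × 7.849 / 4 = 18.8, so 19 (20 t-based).

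Under each variant the calculation still concerns a 2-log difference in means.

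**4. Outcome against inputs.**

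| | Sample size section | Primary outcome and arms |
|---|---|---|
| Scale | logs, means with SDs | clinical class from photographs |
| Groups | saline, hypochlorite | hypochlorite (control), triclosan, two citric acid protocols (Planned interventions) |

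No other section connects the two columns.

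**5. What 25 per arm could detect on the primary outcome (illustration, assumed rates).** Treat remission as binary, compare two arms with one two-sided 5% test and make no multiplicity adjustment. With p̄ the mean of p₁ and p₂:

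Power = Φ{[(p₂ − p₁) − 1.960 × √(2p̄(1 − p̄)/n)] / √([p₁(1 − p₁) + p₂(1 − p₂)]/n)}.

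Example with p₁ = 0.30, p₂ = 0.687, n = 25: (0.387 − 1.960 × 0.1414)/0.1304 = 0.84, so power is 80%.

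| Assumed lower rate | Difference for 80% power, 25 per arm | 21 per arm |
|---|---|---|
| 10% | 34.5 points | 38.2 |
| 20% | 37.8 | 41.3 |
| 30% | 38.7 | 42.1 |
| 40% | 38.1 | 41.1 |
| 50% | 36.1 | 38.8 |
| 60% | 32.9 | 35.1 |

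If the class were analysed as a mean score instead, the detectable difference at 25 per arm is 2.802 × SD × √(2/25) = 0.792 × SD. That is 0.48 to 0.79 score units for an assumed SD of 0.6 to 1.0.

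**The case against.** **The article condenses a fuller protocol.** This would answer a missing detail. Here the article makes a positive statement about the basis of the calculation, and the inputs that follow contradict it.

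**The section speaks of quantitative outcomes, so a microbial count was meant.** Perhaps, but the same sentence names DS remission as the basis. A reader might conclude that the inputs are CFU counts. The unit makes that likely, but the documents do not establish it. Local parameters cites reference 11 for the biofilm-area technique and credits microbial sampling to two other references.

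**The effect size comes from the wrong contrast.** A reader might infer that the 2 logs is an observed saline-versus-hypochlorite difference. The text ties only the standard deviations to those groups, and the 2 logs could be a chosen target. Borrowing standard deviations from another comparison is ordinary practice. What stands is that the relevance of 2 logs to these arms is not justified.

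**The error in n is conservative.** True for the log-scale outcome: 21 exceeds the 16 or 17 that the inputs require. It says nothing about DS remission.

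**The size can no longer change.** According to Trial status, clinical results are already being analysed. This limits the remedy to correcting the statement; it does not make the statement right.

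**Conclusion.** The concern holds on the article's own text. The stated 80% power has no basis for the primary outcome, because log-scale inputs cannot describe a photographic classification. Separately, the stated inputs give 16 per group (17 t-based), not 21. For a 2-log difference, power is about 89–90% at 21 and 93–94% at 25 per group. These figures rest only on the article's numbers and a two-group comparison of means.

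A reader might go further and call the trial underpowered for DS remission. The documents do not support that, since they give no remission rate or target difference. The 33 to 39 percentage points needed for 80% power at 25 per arm hold for assumed lower rates of 10% to 60% and one unadjusted test. They show the order of the detectable difference and prove no shortfall. Nor do the documents call for a disclaimer about equivalence to the hypochlorite control: the Study hypothesis section tests for no difference, and no equivalence or non-inferiority claim is planned.

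**What to change.** Rewrite the Sample size estimation section, leaving the 25 per arm as they are:

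- Name the outcome that the standard deviations and the 2-log difference describe. Microbial load is the likely one, but the sponsor must confirm it from the source. If it is confirmed, label it as a secondary outcome.
- Remove the statement that the calculation is based on DS remission.
- Correct the result for the stated inputs: either 16 per group (17 t-based) at 80% power, or the power actually obtained at 21 and 25. If 21 came from another power level, a multiplicity correction or a different SD, state it.
- Say why 2 logs is a relevant difference between the arms of this trial, or say that it was taken as a working target.
- For 25 per arm, give the difference in DS remission or DS score that two arms could show with 80% power. State the assumed rates or SD, and whether the figure allows for multiple comparisons.

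The cost is some rewording and a short calculation, with no extra patients and no change in design. The downside is that the figure for the primary outcome becomes less favourable than the one now printed.

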### Randomization, allocation, and blinding

The study will be double-blind, and to achieve this, each researcher (R) will have an assignment during the experiment: participants will be distributed into groups taking into account a random numerical sequence (on a 1:1:1:1 ratio) generated by a computer; a researcher (R1) who is not involved in the clinical steps will place the patients’ identification numbers in an envelope, using a blinded approach, and also will prepare the products. Another researcher (R2) will be responsible for opening the envelope at the moment of the delivery of the appropriate product to the patients, according to the hygiene protocols, and examine the patients and collect samples. A third researcher (R3) will distribute the protocols and orientate the participant, and finally the researcher R4 will perform blinded statistical analysis of the data. The researchers involved in the clinical steps (R2 and R3) and the patients will not be blinded because of the nature of the intervention. Patients’ allocated interventions will not be revealed until the statistical analysis is completed.

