### Statistical analysis

Data entry and analysis will be conducted in a blinded fashion. The data collected for the groups, prior to adherence to the hygiene protocols, such as age, gender, and grade of schooling, will be compared to ascertain initial similarity. The effect of groups on primary and secondary outcomes will be assessed. When applicable (i.e OHIP-EDENT), pre-treatment values will be applied as a co-variable in the statistical model. The significance level of the tests will be 0.05. Noncompliant participants will be followed up, such as those requiring interruption of one of the hygiene protocols, and to evaluate the significance of protocol deviations. In other words, the statistical analysis will consider the participants according to the treatment received (per protocol), as well as according to the planned treatment (intention to treat (ITT)); the results will be compared.

The data will be analyzed for homogeneity; in the case of non-normal distribution, the Brunner Langer nonparametric test will be used. For the categorical variables (questionnaire) the Friedman test will be applied to compare the different time points, and the Kruskal-Wallis test will be applied to compare the groups. Correlation between the quality of life indices and the quantitative variables will be tested (Pearson correlation coefficient). The Tukey test with Bonferroni adjustment will be used for subgroup analysis. The Dunn post-test test will be used with the Kruskal-Wallis test.

A flowchart of the participants will be prepared for a detailed explanation of the characteristics of the sample and the quantification of quitters and missing participants. This part will provide the number of individuals examined, reasons for exclusion, and the number of recruited, treatment-allocated participants who complete the trial and are included in analysis at the study end. The flowchart will provide the reasons for any deviation from the protocol.

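### The stated 21 participants at 80% power does not follow from the stated inputs (16–17 per group), and the calculation covers one two-group contrast in a four-arm trial

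*Protocol article*

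**What the plan says.** The Sample size estimation section says that the calculation is based on the primary outcome, denture-related stomatitis remission. Its inputs, taken from a previous trial, are "standard deviation of 2.19 (group 1 - saline group) and 1.79 (group 2 - sodium hypochlorite"), with "a 95% confidence interval (bilateral), and a detectable difference of at least 2 logs". The result is "Based on power of 80%, this clinical study requires at least 21 participants". The dropout step follows: "An additional 20% will be added to the planned sample to compensate for possible dropouts, thus resulting in a total of 25 participants". The Abstract and the Planned interventions section make clear that 25 is the size of each of four groups, 100 patients in all, and the randomization is "on a 1:1:1:1 ratio".

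The Study hypothesis is that the protocols do not differ. The Statistical analysis section sets the level ("The significance level of the tests will be 0.05") and names two multiple-comparison procedures: "The Tukey test with Bonferroni adjustment will be used for subgroup analysis", and the Dunn test after Kruskal-Wallis. It does not say which contrasts are primary or how many there are.

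**The concern.** The section gives every input of a standard two-mean calculation and also its result, so the result can be checked, and it does not come out. A fuller protocol or a separate analysis plan could supply a missing assumption, but the statement as printed would still disagree with itself.

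The basis matters as well. A power statement for one comparison of two groups at 5% says little about pairwise comparisons among four arms once these are adjusted. A reader told that the trial has 80% power could over-interpret a null adjusted comparison whose real power is nearer 70%.

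**Working it through.** **Inputs** (Sample size estimation): SD₁ = 2.19, SD₂ = 1.79, δ = 2, two-sided α = 0.05, power 0.80. The 21 is read as per group, because 21 plus 20% leads to 25 and 25 is the group size.

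**1. The plan's figure.** n per group = (z₁₋α/₂ + z₁₋β)² × (SD₁² + SD₂²) / δ².

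- SD₁² + SD₂² = 4.7961 + 3.2041 = 8.0002, so the root mean square SD is 2.00.
- 80% power: (1.96 + 0.8416)² × 8.0002 / 4 = 15.70, so **16**.
- t-test: power is 78.1% at 16 and 80.7% at 17, so **17**. Welch's version also gives 17.
- As a two-arm total this is 32–34. One-sided testing gives 13–14 per group. Neither is 21.
- Power at 21 per group: 88.5% (t) or 90.0% (normal).

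**2. What would give about 21?** None of these is stated in the section.

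- 90% power: (1.96 + 1.2816)² × 8.0002 / 4 = 21.02, which strictly rounds up to 22 (23 by t-test).
- SD of 2.19 in both groups at 80%: 19 (normal) or 20 (t).
- An inflation for a rank test: about 18–20, or 21 combined with SD 2.19 in both groups.
- Bonferroni for three comparisons at 80%: (2.394 + 0.8416)² × 8.0002 / 4 = 20.94, so 21 (23 by t-test).

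**3. Four arms.** Four arms give 4 × 3 / 2 = 6 pairs; this count is derived, not stated. The noncentrality for one 2-log pair is 2 / (2.00 × √(2/n)), which is 3.16, 3.24 and 3.54 at n = 20, 21 and 25. The Tukey critical |t| for four groups with 4(n − 1) degrees of freedom is 2.61–2.63. Power for one such pair:

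| Evaluable per arm | Unadjusted t | Bonferroni t, 3 comparisons | Tukey, 6 pairs | Bonferroni t, 6 pairs |
|---|---|---|---|---|
| 20 | 86.9% | 74.2% | 70.3% | 64.8% |
| 21 | 88.5% | 76.7% | 73.0% | 67.8% |
| 25 | 93.4% | 85.0% | 81.9% | 77.9% |

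For 80% power over six pairs, Tukey needs 25 evaluable per arm and the Bonferroni t-test needs 27.

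**4. Dropout.** 21 × 1.2 = 25.2, given as 25. If 20% were lost, 25 × 0.8 = 20 would remain. Keeping 21 after a 20% loss needs 21 / 0.8 = 26.25, so 27. Twenty-five keeps 21 up to a loss of 4 / 25 = 16%.

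**The case against.** The strongest reply is that nothing is short on the document's own terms. The error in 21 is conservative, since 21 exceeds 16–17, and even 20 completers give 87% power for the single unadjusted comparison. That stands: the first point is an inconsistency in a stated figure, not a shortfall.

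A reader might infer that the plan prescribes an adjusted comparison of all six pairs and is therefore underpowered. The text does not go that far. It assigns Tukey with Bonferroni to subgroup analysis and gives no number of pairs. G1 is labelled the control, so three comparisons with control are equally compatible. The adjusted powers are therefore conditional, and the Tukey column is plain Tukey, since the text does not define how Tukey and Bonferroni are to be combined.

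A reader might also infer that 21 was really computed at 90% power. The match is close, but 21.02 rounds up to 22, and a three-comparison Bonferroni at the stated 80% also gives 21. The source of 21 cannot be determined from the document.

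Finally, a reader might infer that the trial falls below its own minimum under its assumed dropout. The section adds 20%; it does not state an expected loss of 20%, and 25 is what that sentence describes apart from rounding 25.2 down. The wording that calls 25 a total is loose, but the Abstract and Planned interventions resolve it.

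**Conclusion.** The point holds in this form. The 21 at 80% power is wrong as written: the stated inputs need 16 (normal) or 17 (t) per group, a gap of 4–5 that is not rounding, and 21 per group gives about 88.5% power for one unadjusted comparison.

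The calculation as described rests on one two-group contrast at 0.05, while the trial has four arms and leaves its primary contrasts unnamed. On the assumption that all six pairs are tested with adjustment, 21 per arm falls short of 80% (68–73%), 20 gives 65–70%, and the enrolled 25 is about adequate (78–82%) only if nobody is lost.

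The dropout arithmetic is a minor matter, with consequences mainly under that same assumption.

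All these powers concern a 2-log difference. The primary outcome under Study outcomes is scored by a classification of palatal photographs, so none of them is power for that outcome as it will be measured.

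**What to change.** Keep 25 per group and restate the figures in Sample size estimation:

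- Either give the assumption that produces 21, or state that the inputs need 16–17 per group at 80% power for one unadjusted two-group comparison.
- Name the pairwise comparisons intended, and give power for 25 enrolled and 20 evaluable per arm: 93% and 87% unadjusted and, as a conditional figure, about 82% and 70% under Tukey if all six pairs are meant.
- Replace the total of 25 by 25 per group, 100 in total. This matters because the Data management section ends the study when the target sample size is reached.
- If 21 is kept as the minimum, say that 25 retains it only up to 16% loss.
- Say that these figures apply to a log-scale outcome, whereas the primary outcome is measured by classification scores.

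The cost is wording only. Enrolment does not change, and the Trial status section says that clinical results are already being analysed. The downside is that the stated power for adjusted comparisons becomes less favourable.
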